### 2.4. Functional Assessment of Patients

Functional tests will be carried out on three interspersed days one week before the start of the exercise program, and the tests will coincide with the days that patients received their HD treatment. Patients will be scheduled half an hour before their treatment to perform the corresponding functional tests.

All tests will be repeated when the exercise program is finished at 12 weeks.

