### 2.8. Statistical Analysis

The sample size of the study was calculated using the statistical program G-Power (analysis of variance (ANOVA): repeated measures, within/between interaction), assuming a type I error or α of 0.05 (95% confidence interval), a statistical power of 0.80 (type II or β error), and an effect size of 0.25 (mean), requiring the inclusion of 24 patients to ensure the external validity of the study. Considering that there may be losses during the study follow-up, 80 patients will be included: 40 in the control group and 40 in the intervention group.

Intention-to-treat statistical analysis will be performed using the statistical program SPSS 23.0 for Windows (SPSS Inc, Chicago, IL, USA).

The normal distribution of the groups will be verified through the chi-square and Mann–Whitney U tests for correct randomisation.

A mixed two-way ANOVA test will be used to analyse the effect of the VR exercise on functional variables and inflammatory variables in each study group and to analyse the differences between the two groups.

Data will be presented as mean ± standard deviation, setting statistical significance at *p* < 0.05.

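### With one baseline and one 12-week value, the planned mixed ANOVA compares VR with pedalling through change scores; adjusting for baseline would estimate the same effect more precisely at no cost

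*Protocol article*

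**What the plan says.** Section 2.8 (Statistical Analysis) fixes the method: "A mixed two-way ANOVA test will be used to analyse the effect of the VR exercise on functional variables" and on inflammatory variables, both within each study group and for the difference between the groups. It does not say which term of the ANOVA carries the between-group conclusion. The sample size in the same section was calculated for "analysis of variance (ANOVA): repeated measures, within/between interaction", which points to the group-by-time interaction. No adjustment of the 12-week value for baseline is mentioned.

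Section 2.4 (Functional Assessment of Patients) sets the measurement times: "Functional tests will be carried out on three interspersed days one week before the start of the exercise program" and "All tests will be repeated when the exercise program is finished at 12 weeks". Each functional outcome therefore has two values per patient. For the inflammatory markers, section 2.5 gives no sampling times; a baseline is only implied by the decrease expected in sections 2.2.3 and 3. Section 2.8 does not name the mixed ANOVA for the psychological scales.

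**The concern.** A two-group, two-time mixed ANOVA yields three tests, and only one of them is a sound comparison of the arms:

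- The time effect does not compare treatments.
- The group main effect compares each patient's average of the pre- and post-treatment values. The arms do not differ before treatment except by chance, so this halves the effect.
- The group-by-time interaction is the comparison of mean change.

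A change score subtracts the whole baseline value, however weakly baseline predicts follow-up. When the correlation is moderate, this adds baseline noise to the estimate. A model for the 12-week value with baseline as a covariate lets the data set the weight. It also corrects for chance imbalance in the outcome at baseline.

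Precision matters here because the comparator is active. Sections 2.3 and 2.2.3 give the pedal group the same frequency, duration, perceived exertion and muscle groups, and section 3 expects both groups to improve. The contrast is between two programmes that are both expected to work, so a small difference is plausible.

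**Working it through.** **Inputs from the protocol article.** Two groups of 40, N = 80, alpha 0.05, power 0.80, effect size 0.25 and required N of 24 (section 2.8); two time points (section 2.4).

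**Assumed, because the article gives no value.** Baseline to 12-week correlation rho of 0.3 to 0.7; equal SDs at both times; a 0.5 SD between-group difference for illustration; all 80 patients analysed.

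**Step 1: the plan's own sample size.** Read 0.25 as Cohen's f under the G*Power default for the within/between interaction. The noncentrality is N·m·f²/(1 − rho), with 1·(m − 1) and (N − 2)(m − 1) degrees of freedom, where m is the number of measurements.

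- N = 24 is obtained with m = 4 and rho 0.5 (power 0.816), with m = 3 and rho 0.6, or with m = 2 and rho 0.66 to 0.68 (power 0.810 to 0.833).
- With m = 2 and rho 0.5, N = 34 is needed; N = 24 gives power 0.649.

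The article states neither m nor rho, so the figure reproduces only under unstated settings. That does not affect the present point.

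**Step 2: the interaction is the change-score test.** In a simulated data set of 40 + 40, the group-by-time F and the squared t on change scores were both 1.7551. The two are algebraically identical.

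**Step 3: variance of the treatment estimate,** in units of SD², each multiplied by 4/N:

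- change score: 2(1 − rho)
- baseline-adjusted: 1 − rho²
- ratio of adjusted to change: (1 + rho)/2, a reduction of (1 − rho)/2

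| rho | Change | Adjusted | Reduction | N by the planned method that equals 80 adjusted |
|---|---|---|---|---|
| 0.3 | 1.40 | 0.91 | 35% | 80 × 1.40/0.91 = 123 |
| 0.5 | 1.00 | 0.75 | 25% | 80 × 1.00/0.75 = 107 |
| 0.7 | 0.60 | 0.51 | 15% | 80 × 0.60/0.51 = 94 |

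Allowing for the one degree of freedom spent on the covariate at N = 80, the reductions are 34%, 24% and 14%. In 10,000 simulated trials per correlation they were 34.7%, 24.4% and 13.9%. The mean estimates agreed for a true 0.5 SD (for example 0.497 and 0.498 at rho 0.5), so both methods target the same effect.

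**Step 4: sensitivity.**

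- At rho 0.8 and 0.9 with equal SDs, the reduction is 10% and 5%.
- With a follow-up SD s times the baseline SD, the reduction is 1 − s²(1 − rho²)/(1 + s² − 2·rho·s). For rho 0.7 to 0.3 this is 2 to 22% at s = 1.25 and 37 to 50% at s = 0.8.

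**Step 5: power for an assumed 0.5 SD difference** (noncentral t, N = 80). SE is the square root of the Step 3 variance times 4/80.

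| rho | SE change | SE adjusted | Power change | Power adjusted | Difference detectable with 80% power (SD), change → adjusted |
|---|---|---|---|---|---|
| 0.3 | 0.265 | 0.213 | 46% | 64% | 0.75 → 0.61 |
| 0.5 | 0.224 | 0.194 | 60% | 72% | 0.63 → 0.55 |
| 0.7 | 0.173 | 0.160 | 81% | 87% | 0.49 → 0.45 |

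The group main effect estimates only 0.25 SD, with variance (1 + rho)/2 × 4/80. Its power is 28% at rho 0.3 and 22% at rho 0.7.

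**Step 6: power at the protocol's own effect.** With m = 2, f = 0.25 means a difference in mean change of 4 × 0.25 = 1.0 SD. At N = 80 and rho 0.5 the noncentrality is 80 × 2 × 0.0625/0.5 = 20, and the planned test has about 99% power.

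**The case against.** The strongest reply is that nothing is wrong with the planned test. Under randomisation a change-score comparison is unbiased with correct type I error, and it matches the term on which the trial was sized. That stands. A reader might infer from the concern that the analysis is biased or invalid; the documents do not support that.

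A reader might also infer that the trial is underpowered. Step 6 shows otherwise at the protocol's own effect size. The 0.5 SD difference is a reviewer's illustration, not a protocol figure, and section 2.8 expects losses without giving a rate, so the power figures for 80 patients are a best case for both methods.

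The 15 to 35% range is not a property of this trial. It depends on a correlation and an equality of SDs that the article does not give. If N = 24 was obtained with two measurements, the implied correlation of 0.66 to 0.68 puts the gain at 16 to 17%, near the low end.

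Nor would the two analyses give the same result in one trial. They share the estimand, but in simulation single-trial estimates differed with an SD of 0.16, 0.11 and 0.07 SD units at rho 0.3, 0.5 and 0.7, so p-values can differ too. This is a reason to settle the choice before the data are seen.

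Finally, the ANOVA also serves the within-group question, and section 1 places the comparison with pedalling under the secondary objective. Discarding within-group results would therefore lose something planned. This stands and shapes the fix.

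**Conclusion.** The point holds as a matter of efficiency, not as an error. The group-by-time test is a change-score test (exact, given two time points), and the group main effect should not be used to compare the arms. Adjusting for baseline estimates the same effect with about 15 to 35% less variance, on the assumptions of correlation 0.3 to 0.7 and similar SDs. The gain shrinks to 5 to 10% at correlation 0.8 to 0.9, and to 2 to 22% if the follow-up SD is 1.25 times the baseline SD. In all these cases adjustment has the smaller variance, before the cost of one degree of freedom.

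The benefit is a narrower interval and more power for differences smaller than the 1.0 SD implied by the sizing. The baseline is explicit for the functional tests; for the inflammatory markers the conclusion depends on a pre-programme sample being taken, which the article only implies.

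**What to change.** In section 2.8, state that the between-group comparison of each functional and inflammatory outcome will use a model of the 12-week value on arm, adjusted for the same outcome's baseline. A mixed model that constrains the arms to a common baseline mean would also serve. Report the adjusted difference with its 95% CI. Keep the within-group changes as descriptive estimates, so that the planned description of each programme is not lost. The same model can be used for the scored psychological scales (STAI, BDI-II) where a baseline is taken.

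The cost is a sentence or two in the analysis section. For the functional outcomes no further patients or measurements are needed; for the markers and scales the model uses a baseline value where one is taken.

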Recently, the integration of VR into traditional physical exercise and rehabilitation programs has aroused great interest in the fields of kinesiology and public health. Using VR, it is possible to intensify repetitive tasks and increase visual and auditory feedback, which makes it a novel and attractive therapeutic tool that can be combined with traditional physiotherapy, as it is safe and effective for the patients who use it [32].

Researchers have recently begun to investigate whether the beneficial effects that VR has been shown to have in exercise programs for other populations can be extrapolated to patients with CKF undergoing HD treatment. There are five clinical trials published to date [33,34,35,36,37], the results of which show that the application of VR exercise during HD improves physical function and reduces fatigue and depression in these patients.

In 2019, Segura-Orti and García-Testal conducted a review that reinforced these results, concluding that intradialytic exercise with VR is safe and improves physical function and health-related quality of life in patients on HD. They also concluded that this exercise can be performed safely during the last hours of the HD session [38].

Along the same lines, another review by Olumuyiwa et al. concludes that the use of VR during HD treatment significantly improves the levels of physical activity and fatigue in patients with CKF, as well as increases the levels of adherence and commitment to HD treatment, without the appearance of adverse effects [39].

Currently, only one study has analysed the effect of VR exercise on depression levels in patients on HD, whereas the effect of VR exercise on the inflammatory status of these patients has not been studied at all. It could be expected that the beneficial effects on inflammation are comparable to those obtained with conventional exercise [19], and their psychological state also improves. Therefore, we plan to carry out a study of these characteristics with the aim of determining the effectiveness of an intradialytic exercise program with VR on inflammatory markers, in addition to delving into its effect on functional capacity and psychological state. As a secondary objective, we intend to analyse the levels of adherence to the exercise program and compare the results obtained for all the variables to those of a group that performs intradialytic static pedal exercise.

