#### 2.2.3. Description of the Intervention

An intradialytic exercise program with non-immersive VR will be carried out for 12 weeks with the aim of improving the functional capacity of patients with CKF, as well as their psychological state (decreased anxiety and depression) and inflammatory state (decreased inflammatory markers IL-6, TNF-α, CRP, ICAM-1, and VCAM-1). For its execution, a sample of 80 subjects from the Haemodialysis Unit of the Balmis Hospital in Alicante will be selected, and the sample will be randomized into two groups (intervention group and control group). The intervention group (n = 40) will perform intradialytic exercise with non-immersive VR. The control group (n = 40) will perform intradialytic exercise with a static pedal.

As the health benefits of exercise in patients with CKF have been widely demonstrated [17,18,19], it would not be ethical to deprive one of the groups of exercising. Therefore, it has been decided that the control group will perform an intradialytic exercise with a static pedal, which will exercise the same muscle groups as in the intervention group with VR.

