## 4. Conclusions

VR can improve the level of adherence to exercise in patients on HD. This means that the patients perform a greater number of exercise sessions than with conventional exercise, giving rise to a greater effect of the VR exercise on the inflammatory state, functional capacity, and psychological state of the patients; thus, this enhances their health-related quality of life and improves their cardiovascular morbidity and mortality.

In addition to these benefits, VR can also liven up the HD sessions for patients, making CKF more bearable for patients who undergo 4 h treatments three times a week.

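### One p < 0.05 rule covers about 16 outcomes, none of them primary, and the stated aims conflict, so the chance of a false-positive arm difference is well above 5%

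*Protocol article*

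**What the plan says.** **Decision rule.** Section 2.8 states: "Data will be presented as mean ± standard deviation, setting statistical significance at" p < 0.05. It names a mixed two-way ANOVA for the functional and inflammatory variables. The Introduction extends the comparison with the pedal group to every variable studied. Section 2.6.1 has its own p < 0.05 criterion for a pre-to-post change in CAMAE-RD.

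**Sample size.** Section 2.8 uses the G-Power model for "analysis of variance (ANOVA): repeated measures, within/between interaction", "assuming a type I error or α of 0.05 (95% confidence interval), a statistical power of 0.80", with "an effect size of 0.25 (mean), requiring the inclusion of 24 patients". It does not say which variable the 0.25 refers to.

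**Aims.** Three places rank them differently:

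- Introduction: the aim is "determining the effectiveness of an intradialytic exercise program with VR on inflammatory markers". Function and psychological state come in addition, and adherence and the arm comparison are labelled a secondary objective.
- Section 2.2.3: the programme is run "with the aim of improving the functional capacity of patients with CKF, as well as their psychological state", with inflammatory state named last.
- Section 4: the opening claim is "VR can improve the level of adherence to exercise in patients on HD", and the gains in the other domains are derived from it.

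**The concern.** An alpha of 0.05 describes the trial's error rate only if one pre-named test carries the claim. Here the text does not say which test that is. The Introduction comes closest, but its leading aim covers five markers without ranking them. Sections 2.2.3 and 4 put other domains first, and the sample-size statement does not settle the matter. With a flat 0.05 on every outcome, the trial could report an arm difference in inflammation, function, mood or adherence and cite a section of its own protocol in support. The error rate of such a claim would be several times the one stated.

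**Working it through.** **1. The plan's own figure.** I checked whether the 24 patients point to a particular outcome. For two groups, m measurements and correlation ρ between them, power for the interaction comes from a noncentral F with λ = f²·N·m/(1−ρ), df1 = m−1 and df2 = (N−2)(m−1), with f = 0.25.

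- m = 4, ρ = 0.5: λ = 0.0625 × 24 × 4 / 0.5 = 12, power at N = 24 is 0.816, required N = 24.
- m = 3, ρ = 0.6: required N = 24.
- m = 2, ρ = 0.5: λ = 6, power at N = 24 is 0.649, required N = 34.
- m = 2, ρ = 0.65: power at N = 24 is 0.799, required N = 26.

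Section 2.4 describes two occasions for the functional tests, before the programme and again afterwards ("All tests will be repeated when the exercise program is finished at 12 weeks"). The 24 can therefore be reproduced only under values of m and ρ that the article does not state, and nothing in it identifies an outcome.

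**2. Number of outcomes.**

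- Functional (section 2.4): SPPB, one-leg balance, Timed Up and Go, STS-10, STS-60, six-minute walk = 6.
- Inflammatory (section 2.5): IL-6, TNF-α, CRP, ICAM-1, VCAM-1 = 5.
- Psychological (section 2.6): CAMAE-RD, STAI-E, STAI-R, BDI-II = 4.
- Adherence (section 2.7) = 1.

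The total is 6 + 5 + 4 + 1 = 16. The ANOVA is named for 6 + 5 = 11 of these. SPPB components, CAMAE-RD areas and the 75% adherence category are not counted.

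**3. Chance of at least one false-positive arm difference.** I assume no true difference on any outcome and two-sided tests (the article does not state sidedness). For n independent tests the chance is 1 − 0.95ⁿ. If only results favouring VR count, it is 1 − 0.975ⁿ.

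| Tests | Either direction | Favouring VR only |
|---|---|---|
| 1 | 5.0% | 2.5% |
| 5 markers | 1 − 0.95⁵ = 22.6% | 11.9% |
| 11 with a named ANOVA | 1 − 0.95¹¹ = 43.1% | 24.3% |
| 16 | 1 − 0.95¹⁶ = 56.0% | 1 − 0.975¹⁶ = 33.3% |

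The expected number of false positives over 16 tests is 16 × 0.05 = 0.8.

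**4. Correlated outcomes.** The article gives no correlations, so these are assumed values (simulation with 200,000 draws, 16 tests, either direction).

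| Structure | Correlation | Chance |
|---|---|---|
| Equal across all 16 | 0.1 | 54.9% |
| | 0.3 | 47.5% |
| | 0.5 | 37.2% |
| Within domains only (6/5/4/1) | 0.3 | 53.1% |
| | 0.5 | 48.1% |
| | 0.7 | 41.2% |

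For results favouring VR with equal correlation across all 16, the chance is 24.4% at 0.3 and 18.7% at 0.5.

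**The case against.** Several points for the plan stand.

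- **It does state some hierarchy.** The Introduction makes adherence and the arm comparison secondary. It would be wrong to say that the article ranks nothing, or that every section leads with a different aim. The Abstract and section 2.2.3 both put function first, and section 3 opens with inflammatory markers and brings in adherence only in its second sentence. The conflict is between the Introduction, section 2.2.3 and section 4.
- **A multiplicity procedure may sit in an analysis plan that is not shown.** Its absence here is therefore not the finding. An analysis plan could add an adjustment, but it would not remove the conflict between the aims printed in the protocol.
- **The 16 arm comparisons are partly inferred.** Section 2.8 names a test for only 11, and the CAMAE-RD criterion concerns change over time. The other five rest on the Introduction's comparison of every variable and the general 0.05 rule.
- **Not every ANOVA p-value bears on VR.** Section 3 expects improvement over time in both arms, so a time effect is not a false effect of VR, and I have not counted it.

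A reader might infer that a spurious benefit of VR is more likely than not. The documents do not support that. Passing 50% takes at least 14 independent tests (13 give 48.7%, 14 give 51.2%) and counts errors in either direction. Related measures such as STS-10 and STS-60, or the two STAI scales, are unlikely to be independent. A reader might also infer that the sponsor will claim success on any single outcome. That is not written; section 3 expects a pattern of higher adherence with greater effects across the variables.

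**Conclusion.** The point holds in this form: a flat 0.05 applies to about 16 outcomes, none is singled out, the sample size is linked to none, and three parts of the article disagree on the lead aim. The chance of at least one false-positive arm difference in either direction is about 37% to 56% over 16 outcomes, for equal correlations from 0.5 down to 0. For independent tests it is 43% over the 11 outcomes with a named ANOVA and 23% over the five markers. Counting only results in favour of VR, 16 independent tests give 33%, against 2.5% for a single test. All these figures assume no true difference on any outcome, and the correlations are my assumptions. Even the narrowest reading, in which only the Introduction's five markers count, gives more than four times the stated 5% if they are independent (22.6 / 5 = 4.5).

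**What to change.** 1. Reconcile the aims in the Introduction and sections 2.2.3, 3 and 4. This includes the Introduction's labelling of the arm comparison as secondary, because the sample-size model in section 2.8 is itself an arm-by-time interaction.
2. Designate one confirmatory between-arm contrast at 12 weeks, consistent with the Introduction's first-named aim. IL-6 is one example, on whichever scale the sponsor pre-specifies; the Introduction describes it as a better predictor of mortality than CRP and other cytokines. The choice is the sponsor's. Test only that contrast at 0.05.
3. State which outcome the effect size of 0.25 refers to, with the assumed number of measurements and their correlation.
4. Make all other markers, the functional tests, the four psychological scores and adherence secondary. Either apply Holm adjustment across them, or report estimates with 95% confidence intervals and make no confirmatory claim.

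**Cost.** Mostly wording, plus alignment of the registry entry. Fewer results may be called significant. Expressing the effect size in units of the chosen outcome would need a standard deviation and a target difference that the article does not give. The planned 80 patients leave room for adjustment: with two measurements and an assumed correlation of 0.5, Bonferroni over all 16 (0.05 / 16 = 0.003125) needs 64 patients for f = 0.25, and 80 analysed patients give power 0.918. Holm is never less powerful than Bonferroni.

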## 3. Expected Results

Both exercise groups (with non-immersive VR and with a static pedal) are expected to see a decrease in their levels of inflammatory markers and improvement in their functional capacity and psychological status. However, higher levels of adherence are expected in the VR group, which will have greater effects on the variables studied in the VR exercise group than in the static-pedal-exercise group.

## 4. Conclusions

VR can improve the level of adherence to exercise in patients on HD. This means that the patients perform a greater number of exercise sessions than with conventional exercise, giving rise to a greater effect of the VR exercise on the inflammatory state, functional capacity, and psychological state of the patients; thus, this enhances their health-related quality of life and improves their cardiovascular morbidity and mortality.

In addition to these benefits, VR can also liven up the HD sessions for patients, making CKF more bearable for patients who undergo 4 h treatments three times a week.

